## **Study objectives**

The main part of this study aims to determine patient preferences for and satisfaction with consent procedures regarding the use of residual tissue for research, to provide insight into the type of information patients need to decide on the use of their material in research, and to determine the optimality of the timing and the content of these procedures in clinical practice. We will compare the three consent procedures, opt-out, opt-out plus and informed consent, with respect to the following primary study outcomes:

1. Patients' satisfaction with and preference for a consent procedure
2. Proportion of patients aware of storage of tissue and research use
3. Consent rates
4. Medical staff's satisfaction with and preference for a consent procedure

Additionally, we will obtain information on (1) the proportion of non-consent due to non-response; (2) the characteristics of non-consenters and non-respondents; and (3) the reasons for providing or withholding consent or (non-)response. We will investigate how patients perceived the information they received about residual tissue use and their knowledge about this topic. Patients' preferences to provide or withhold consent for specific types of research (e.g. genetic, commercial) and feedback regarding unanticipated findings will be investigated as well. Further, we will examine whether consent rates, satisfaction with or preference for a consent procedure differ according to severity of disease, type of clinical procedure (e.g., biopsies or surgical removal of tissue), diagnosis, type of hospital (academic or community) or demographics. Six months after the first questionnaire, we will examine whether patients are still aware of the decision they made and whether they are still satisfied with their choice to provide or withhold consent.

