### **Study design including study arms**

In this multicentre randomized controlled trial, 1800 patients will be recruited from academic and community hospitals during an 18 month period (Figure 2). The consent procedures will be offered a short time before or after the tissue or blood is removed, dependent on what is the best timing according to the clinician or nurse practitioner. Patients to be included are

distributed over four hospitals: two academic hospitals and two regional hospitals: the NKI-AVL, the Vrije Universiteit Medical Center (VUmc), the Spaarne hospital in Hoofddorp and the Kennemer hospital in Haarlem. Inclusion of academic and community hospitals will increase the external validity (i.e. generalizability) of the study results.

Patients will be randomized, stratified by hospital and diagnosis, to opt-out plus, informed consent or opt-out (control group) in collaboration with [name] (statistician NKI-AVL). Clinicians and nurse practitioners who will carry out the intervention will receive envelopes that each contain the paperwork (checklist, brochure in opt-out plus and informed consent arms and return envelopes) for one patient. The envelopes will be put in order of the randomization. Clinicians and nurse practitioners will write down his or her name, the patient's name, patient number, diagnosis, date and method of tissue removal on the checklist. A random selection of diagnoses on the checklists will be compared with the diagnoses in the medical files to check their validity. If the validity is found to be poor, all diagnoses will be checked.

In our previous intervention study (see preliminary results) we asked patients informed consent before the start of the intervention. However, patients felt that it was confusing to be asked informed consent for a study in which they were asked to provide informed consent. To prevent this kind of confusion in the current study, we will not ask consent for the randomization and the intervention. We believe that not asking consent for the randomization is suitable to our study because the informed consent procedure bears no potential harm to the participants, the intervention is of importance for future clinical research, the intervention includes no invasive procedure for the participants, and at least the standard care is offered to participants in the control group.

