### ***Sample size, statistical power***

Sample size is based on an expected response of 75%, allowing sufficient power to address the major outcomes, i.e. consent rates and preferences for procedures, in different subgroups of e.g. hospitals, age and gender. In order to test the hypothesis that the two interventions result in a difference of at least 10% in consent rates, 0.1% non-consent in the opt-out plus or opt-out group versus 10% in the informed consent group, 121 patients per group are needed (80% power and a 2-sided alpha of 0.05; with continuity correction). The difference of 10% is based on our earlier research and the difference is considered a relevant loss of patient materials for research which may lead to selection bias. Because the setting of diagnosis and treatment is different between surgical and outpatient settings and also between general and academic hospitals, it is important to be able to compare the responses in these subgroups. We have also shown in our earlier studies that educational level is associated with preference for a certain procedure and this may also drive response rates of patients. Therefore we propose to include in each intervention group up to 600 patients to be able to conduct subgroup analysis and include adjustment factors; with a response rate of 75% and hence with 450 participants per group we could stratify for 3 to 4 factors, i.e. 90-150 per subgroup, and still have enough power to investigate a difference in response rate of 0.1% versus 10%. Patients will not be stratified by education or sex; we expect these two factors to be equally distributed across groups.

Another reason to obtain a large sample size is that the percentage of non-consenters is small, while it is important to assess their opinions and reasons for non-consent. In the earlier intervention study, 4.6% of respondents indicated in the questionnaire that they wanted to withhold consent or that they did not know whether they wanted to. A sample size of 1800 patients and a response rate of 75% will lead to approximately 62 patients who want to withhold consent or are not sure which choice to make.

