## ***Basic plan of analysis***

Analysis will first be performed to evaluate the comparability of the intervention groups and the control group at study entry in terms of sociodemographic and clinical characteristics. Student's t-test or appropriate non-parametric statistics will be used, depending on the level of measurement. If the groups are found not to be comparable on one or more background variables, those variables will be employed routinely as covariates in subsequent analyses using multivariate models, such as logistic regression.

The proportion of the outcomes in each intervention arm, i.e. consent rates and patients' satisfaction with and preference for a consent procedure, the proportion of patients aware of storage of tissue and research use, and the satisfaction with and preference for a consent procedure of the medical staff, will be evaluated by comparison of the informed consent

versus the opt-out plus group, and the opt-out plus versus the opt-out group by non-parametric or parametric tests as appropriate. Patient characteristics, satisfaction with and preferences for the information and consent procedures will be evaluated according to patient characteristics such as age, educational level, sex, hospital type, type of clinical procedure, and disease type. All analyses will be performed using SPSS.

A qualitative analysis of the information needs and appreciation of the patients for the consent procedures will be evaluated through questions in the questionnaire and telephone interviews with a representative group of patients who completed the questionnaire.

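### Hospital type is handled as a patient characteristic, but with two hospitals per type it cannot be separated from the individual hospitals, so a patient-level comparison can mistake hospital-to-hospital variation for a type effect

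*Protocol*

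**What the plan says.** The Study design section of the protocol has patients "distributed over four hospitals: two academic hospitals and two regional hospitals", individually randomised to three arms and stratified by hospital and diagnosis.

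The Study objectives list, after the primary outcomes, an examination of whether consent rates, satisfaction or preference differ by several factors, including "type of hospital (academic or community) or demographics".

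The Basic plan of analysis says that satisfaction and preferences "will be evaluated according to patient characteristics such as age, educational level, sex, hospital type", followed by type of clinical procedure and disease type. The methods named anywhere in that section are the t-test or non-parametric statistics for baseline comparability, logistic regression for covariate adjustment, and parametric or non-parametric tests for the arm contrasts. No hospital term, random effect or other allowance for clustering is mentioned.

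The Sample size section gives as one reason for up to 600 patients per arm that settings differ, "also between general and academic hospitals, it is important to be able to compare the responses in these subgroups". It adds that with 450 respondents per arm "we could stratify for 3 to 4 factors, i.e. 90-150 per subgroup" while keeping power for 0.1% versus 10%.

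**The concern.** Age, sex and education vary between patients of the same hospital. Hospital type does not: it takes one value per hospital and is replicated twice at each level. The number of independent observations behind an academic-versus-community contrast is therefore two against two, however many patients each hospital enrols.

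Hospitals commonly differ in how staff deliver information, how local leaflets read and how forms are followed up. If such differences exist, a patient-level analysis with a hospital-type term attributes them to type and uses a standard error that is too small. This would remain true if all four hospitals enrolled identical patients, so adjustment for case mix does not remove it. Case mix is a further difficulty here: one academic hospital includes malignant conditions only, and the other excludes colorectal and malignant head/neck conditions.

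At stake is a conclusion that academic and community patients differ in consent, satisfaction or preference, when the data show only that four particular hospitals differ.

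**Working it through.** **The plan's own figures.** The protocol gives no power figure for academic versus community hospitals. Its subgroup range is 450/5 = 90 to 450/3 = 150, that is, patients per arm within a subgroup. The power attached to it is for 0.1% versus 10%, which the same section defines as opt-out (plus) against informed consent. It is an arm contrast inside a subgroup, not a contrast between hospital types. (The 121 per group stated for that contrast does not follow from 0.1% versus 10%, which gives 95 with continuity correction; 1% versus 10% gives 121. That is a separate matter with no bearing here.)

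**Inputs.**
- From the protocol: 1800 patients, 75% response, four hospitals (two per type), 43% preference for opt-out plus from the earlier studies.
- Assumed: an equal split over hospitals, because Figure 1 is not shown. This gives 1800 × 0.75 / 4 = 337.5 respondents per hospital and 675 per type.
- Assumed: an ICC between 0 and 0.05, because the protocol states none.

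**Formulas.** With m respondents per hospital, the variance of the difference between types exceeds the value assumed under independence by the design effect D = 1 + (m − 1) × ICC. The true error rate of a two-sided 5% patient-level test is 2 × [1 − Φ(1.96/√D)]. The between-hospital standard deviation implied at 43% is √(ICC × 0.43 × 0.57).

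For ICC 0.01: D = 1 + 336.5 × 0.01 = 4.37; 1.96/√4.37 = 0.938; error rate 0.348. The 675 respondents per type carry the information of 675/4.37, about 155.

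| ICC (assumed) | Between-hospital SD, points | D | Error rate, all respondents | Error rate, one arm (m = 112.5) |
|---|---|---|---|---|
| 0 | 0 | 1.00 | 5% | 5% |
| 0.001 | 1.6 | 1.34 | 9% | 6% |
| 0.005 | 3.5 | 2.68 | 23% | 12% |
| 0.01 | 5.0 | 4.37 | 35% | 18% |
| 0.02 | 7.0 | 7.73 | 48% | 28% |
| 0.05 | 11.1 | 17.82 | 64% | 45% |

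**Check by simulation** (beta-binomial, 40,000 runs, 337 per hospital): 5.0%, 9.0%, 23.6%, 35.6%, 48.5% and 64.7% in the same order, in agreement with the formula. A t-test on the four hospital proportions (2 degrees of freedom, critical value 4.30) stays at about 5% throughout.

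**What a valid test of type could deliver.** Take, for illustration only, a true 10-point difference in preference between types. The test on four hospital proportions has power of about 53% at ICC 0, 19% at 0.01 and 9% at 0.05. The patient-level test appears to have about 97% at ICC 0. More patients per hospital do not change the two-against-two structure.

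**Arm contrasts.** Each hospital contributes to all three arms, so a hospital effect common to the arms cancels. Simulated error rates for an arm comparison were 4.8%, 5.0% and 4.5% at ICC 0, 0.01 and 0.05.

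**The case against.** Four points can be made for the plan.

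- **No test of hospital type is specified.** A reader might infer that the protocol prescribes a test treating patients as independent. It does not: it says only that results will be evaluated by this and other characteristics, and an analysis plan could add a hospital term. This stands as a limit on the wording. What remains is that the protocol itself places hospital type among patient characteristics and names only patient-level methods. No later model can create more than two hospitals per type.
- **The inflation depends on an unknown ICC.** A reader might infer that chance differences will be declared significant. At ICC 0 there is no inflation and at 0.001 it is modest; the larger rates need between-hospital standard deviations of 5 to 11 points, which the protocol neither supports nor excludes. This stands: the supportable word is "can".
- **The subgroup power is not miscounted.** A reader might infer that 90 to 150 per subgroup is the claimed power for comparing hospital types. It belongs to arm contrasts within subgroups, for which counting patients is right. This stands. The only weakness is that the same paragraph cites comparing responses between general and academic hospitals as a reason for the larger sample.
- **The aim is minor.** Hospital type is in none of the primary outcomes, hypotheses or criteria for choosing a procedure, and the claim of generalisability rests on including both types, not on testing them. This stands and limits the weight of the point. The comparison is nevertheless a stated aim, and the upper age limit was set partly to make such differences interpretable.

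**Conclusion.** The point holds for the academic-versus-community comparison only. With two hospitals per type, type is inseparable from hospital, and a patient-level comparison, the natural but not explicit reading of the plan, can present hospital variation as a type effect. If 337 respondents per hospital and 43% preference are assumed, a nominal 5% test errs in about 9% of cases at ICC 0.001, 35% at 0.01 and 64% at 0.05, and in 5% if hospitals do not vary at all. The ICC and the equal split are assumptions; the two-against-two structure is not. The randomised comparisons, including those within hospital type, are not affected by this problem. It should be corrected, because the correction is cheap and prevents an unsupported conclusion on a stated additional aim.

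**What to change.** **Basic plan of analysis.** Remove hospital type from the list of patient characteristics. Report consent, satisfaction and preference for each of the four hospitals, by arm, with confidence intervals. In models for other characteristics, enter hospital (four levels, already a randomisation stratum) in place of hospital type. Present the academic-versus-community contrast as descriptive, without a patient-level p-value.

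**Sample size.** Keep arm comparisons within hospital type as a reason for the larger sample, but state that additional patients do not give power to compare academic with general hospitals as types.

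**Cost.** Wording only, with no extra patients or data. The price is that the academic-versus-community comparison becomes descriptive.

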## ***Privacy***

Data will be coded according to the standard coding rules of the Division of Psychosocial Research and Epidemiology of the NKI-AVL. The principal investigator (Dr. ir. [name]) and study coordinator (Dr. [name]) will have access to the code. The principal investigator will safeguard the key to the code. Our privacy procedure will comply with the 'code goed gedrag' of the Federa.

## ***Publication policy***

The results will be published in national and international peer-reviewed journals. If applicable, we will publish in the national press in collaboration with the public relations departments of all participating hospitals. Further, if a consent procedure can be developed in accordance with patients' wishes and research needs, we will develop a brochure about secondary tissue use together with the relevant stakeholders, that can be used in this procedure.

## ***Burden for the patients / respondents***

Usual care is offered to patients in the control group. In both intervention groups patients receive brief verbal information and a leaflet, after which they are either asked to sign a consent form or to sign an opt-out form if the patients wants to opt-out. The procedures in the two intervention arms bear no harm to patients. Six weeks after the intervention, patients are asked to fill in a questionnaire. This will take about 45 minutes. 25% of the respondents will be interviewed by telephone, which will take about 20 minutes. Respondents will be sent a second questionnaire, which will take about 10 minutes to fill in. Based on our previous experiences, it is unlikely that the intervention procedures, filling in the questionnaires, or participating in the interview will cause any distress for respondents.

## ***List of attachments***

- A: Detailed information on the background of this study and on previous research
- B: First questionnaire
- C: Second questionnaire
- D: Pre-intervention questionnaire medical staff
- E: Post-intervention questionnaire medical staff
- F: Brochure opt-out plus intervention arm
- G: Brochure informed consent intervention arm
- H: Information leaflet Tissue Issue
- I: Consent form Tissue Issue
- J: Patient letter 1
- K: Patient letter 2
- L: Patient reminder 1
- M: Patient reminder 2
- N: Inserted sheet with pictures of brochures
- O: Checklist medical staff informed consent
- P: Checklist medical staff opt-out plus
- Q: Checklist medical staff opt-out

## Figures

[figure not shown]

**Figure 1: Number of included patients per hospital and condition. Numbers between brackets indicate the expected number of respondents based on a response rate of 75%.**

[figure not shown]

